**Table S2: Sample size to assess non-inferiority of 4RIF efficacy**

*(calculated using alpha=0.05 and one-sided test using methods suggested by Blackwelder 180)*

| **Expected cumulative incidence of TB** | | **Tolerated difference** | | **Number (per group) required to provide power of** | |
| --- | --- | --- | --- | --- | --- |
| **Untreated** | **9INH** | **Δ (25%)** | **Maximum Event rate with 4RIF** | **80%** | **90%** |
| 3% | 0.3% | 0.75% | 1.05% | 658 | 911 |
| 4% | 0.4% | 1% | 1.4% | 493 | 683 |
| 5% | 0.5% | 1.25% | 1.75% | 394 | 546 |

**2.12 Planned recruitment rate:** (see also Section 2.15)

At the Canadian sites, we anticipate 455 subjects enrolled annually, based on an expectation of similar enrolment at continuing sites, and the addition of Vancouver. The Vancouver site is the largest TB clinic in Canada with more than 800 persons treated for LTBI annually. Given the allocation of the same budget as for Montreal and with 33% more patients, it seems realistic to expect similar recruitment rates as in Montreal. We plan to double the capacity in Brazil by doubling staff and doubling the number of clinics at which patients will be enrolled. We anticipate little change in enrolment in Saudi Arabia. Two new sites will be added in West Africa; both have substantial experience and infrastructure for the conduct of randomized trials of active TB. We anticipate a rapid start-up with an average of 500 enrolments annually from both sites (letter from [name] - Appendix 1). In Seoul, Korea four University hospitals and the very busy clinic at the Korean Institute of TB (KIT) will be added, under the direction of [name] (Director of KIT - see letter in Appendix 1). Investigators at KIT were recently awarded a major grant for a 10 year longitudinal study of 3,000 close contacts. It is anticipated that at least 500 contacts with LTBI will be recruited annually at this site. In Australia and Saudi Arabia, the patient volumes are much lower, but addition of these two sites will be valuable because of the high quality TB programmes, and potentially greater generalizability of results to a broader range of settings. In addition both sites will cover all local costs – hence only travel costs for meetings, training, and supervision will be needed (see letters from [name], and [name] - Appendix 1). [name] will spend three months during years 1 and 2 in getting the study initiated at all these sites. (This plan is supported by his department Chair - see [name] letter in Appendix 1). If all sites enrol a total of 1,950 participants annually (see section 2.15), we should complete enrolment within 3 years, although we have planned recruitment over 3.5 years. And, as in Phase 2, enrolment will be monitored closely, and corrective actions taken promptly - including addition of sub-sites, and, if necessary, shifting operating budgets from under-performing sites.

**2.13 Anticipated problems with compliance and treatment completion**

As discussed in Section 2.3, we expect differences in treatment completion to be the major determinant of differences in effectiveness of the two regimens. Our sample size calculations are based on these expected differences in completion rates, so recruitment will not be further increased to account for non-completion of therapy. We do not anticipate a major problem with “drop-ins” 166 during treatment i.e. patients who change therapy and cross over from one arm to the other, as this was seen in less than 1% of subjects randomized in Phase 2. Our planned secondary analysis of efficacy will be based on treatment completion, and assessment of compliance based on pill counting. This measure correlated well with electronic monitoring in Phase 2, and with protective effect in prior trials 65.

**2.14 Loss to follow-up**

Our ability to follow all participants successfully for 28 months after randomization will be crucial. Our objective is to have less than 10% drop-outs; higher rates would be of concern, given the anticipated rate of the primary outcome of less than 3%. Loss to follow-up was 17% in Phase 2, although over 97% of subjects had some follow-up (see RCT Appendix 1: Table 7). Based on experience gained in Phase 2, we will ask for home, work, and cellular telephone numbers, plus email addresses of the study participants, at the time of their enrolment. We will also ask for four other contacts – close friends, or relatives living in the same city, or same country, or relatives remaining in their home country for recently arrived immigrants. This approach has been successful, in another ongoing trial of LTBI therapy at the Montreal Chest Institute, in keeping losses to less than 5% of those randomized, during 33 months of follow-up. The initial consent will include subjects’ permission to verify their occurrence of active TB using local nominal TB reporting databases – for all sites, and provincial health administrative data-bases for Canadian sites. This will provide a mechanism (that we have used 181, 182) to verify occurrence of active TB passively, and assess under-estimation of the study outcome, due to mortality or migration.

**2.15 Description of study centres, and justification for international sites:**

Selection of the international sites has been based on long-standing collaborative ties 172, 183-191, 192 between the site investigators and the PI. All involved countries have a substantial burden of TB, and are classified as having intermediate or °high incidence 2. Inclusion of these sites strengthens the study for several reasons: (i) TB is a global disease that disproportionately affects low and middle income countries, where it is a very high priority health problem. (ii) LTBI therapy is under-utilized in these countries because it is viewed as impractical – but could have important benefits if therapy was simplified. (iii) Conduct of the trial in these international settings may help to demonstrate the feasibility, and cost-effectiveness of this strategy in these settings. This may enhance uptake of the findings in countries with a substantial TB burden. (iv) The training and conduct of this trial will strengthen capacity for clinical research in each country - an important long-term benefit. (v) These sites enhance the feasibility, and cost-effectiveness of the present trial.

**Participating Canadian and international sites in Phase 3.** (*Four will be new sites. **Brazil will double clinic sites)

|  | Number of patients treated per year (from 2005-2007) | | Eligible per year, (estimated for new sites) | Annual enrolment | |
| --- | --- | --- | --- | --- | --- |
| Active TB | LTBI |  | Phase 2 | Projected |
| Montreal Chest | 60-70 | 550-650 | 200 | 140 | 150 |
| Saskatoon | 80-90 | 300 | 50 | 25 | 30 |
| Toronto | 60-70 | 250-300 | 50 | 25 | 50 |
| Edmonton | 70 | 450 | 100 | 60 | 75 |
| Vancouver* | 120 | 800 | 250-300 | -- | 150 |
| Rio de Janeiro, Brazil** | 800 | >1,000 | >500 | 180 | 350 |
| Riyadh, Saudi Arabia | 100 | 300 | 150 | 70 | 70 |
| Korea* | 2560 | na | 2500 | na | 500 |
| Australia* | 300 | 123 | 120 | na | 75 |
| Benin* | >1,000 | na | 500 | na | 250 |
| Guinee* | >1,000 | na | 500 | na | 250 |
| TOTAL | >2,000 | > 4,000 | > 1,600 | 500 | 1950 |

**2.16 Primary data analysis**

The primary study outcome will be the occurrence of microbiologically or histologically confirmed active TB, confirmed by the majority of the 3-member independent clinical review panel. The primary analysis, comparing the rate of occurrence of active TB per patient-year will be performed with the use of an unadjusted Poisson marginal model fitted using generalized estimating equations (GEE) to allow us to take clustering by household into account 193, 194. We will assume an exchangeable correlation structure. The log of follow up time will be used as an offset in the regression model, which will allow us to account for differing lengths of follow up time 194 If clustering is significant we will calculate a rate ratio from the GEE Poisson regression. But if the effect of clustering is negligible, as anticipated, the proportion of subjects randomized to both treatment groups developing confirmed active TB, and the associated 2-sided 95% confidence interval for the difference, will be estimated, using an incidence density method, expressed as TB events per 1000 person years of follow-up. This will allow us to include information from subjects who are followed for some time before being lost to follow-up.

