**SECTION 2 THE PROPOSED TRIAL**

**2.1 Study design**

We propose a multi-centre randomized 2-arm positive control open-label clinical trial. Patients prescribed standard therapy for LTBI (i.e. 9 months INH) will be approached to participate before they begin therapy. After providing informed consent, subjects will be registered using a web-based system, accessible at all times. This system will verify eligibility and perform immediate on-line randomization, using a computer generated random sequence, in equal numbers to 4RIF or 9INH - both daily and self administered. Randomization will be stratified by site and in blocks of variable length. The primary end-point will be the occurrence of microbiologically confirmed active TB. Secondary end-points include occurrence of confirmed and probable active TB, Grade 3 or 4 adverse events (SAE), drug resistant active TB, and health system costs. All primary outcomes will be reviewed by an independent 3-member clinical review panel, and all SAE will be reviewed by a different independent 3-member panel. Both panels will be blinded to the study drug, and patient identity.

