**2.11 Sample size requirements**

Our primary objective is to test whether 4RIF has superior effectiveness compared to 9INH in reducing occurrence of confirmed active TB, based on a planned intention to treat analysis. The number required depends upon the estimated rate of active TB in treated, and untreated patients, and the expected completion rates with 9INH. The expected rate of TB is hard to predict, since we will enrol patients at a wide range of increased risk. In the international sites, where most patients will be contacts (risk over 2 years of 3% 62 174 up to 8-10% 63, 175), or HIV infected (**annual** risk 3-8% 20, 21), cumulative incidence if untreated (or non-compliant) should exceed 5%, but may be only 2% in untreated subjects in Canada. Hence we assume an average cumulative incidence of 3% among untreated. Based on the assumption that 9INH has 90% efficacy if completed 140, but only 50% completion rate 70, 93, 96-102, and 4IRF efficacy is 90% the required sample size, calculated using Poisson distribution, would be 2,898 participants with full follow-up in each group (see Table S1 below). If re-calculated using the binomial distribution (and [*http://stat.ubc.ca/~rollin/stats/ssize/b2.html*](http://stat.ubc.ca/~rollin/stats/ssize/b2.html)) the sample size required would be 2% to 5% larger. Smaller differences in completion will reduce power, but higher event rates (that are certainly plausible) will substantially increase power.

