**Table S1: Sample size required to detect superior effectiveness of 4RIF compared to 9INH**

*(calculated using Poisson distribution 176, assuming alpha=0.05 and two-sided tests)*

| **Expected cumulative incidence of TB**  **over 28 months after randomization** | | | **N (per group) to detect difference,**  **with power of:** | | |
| --- | --- | --- | --- | --- | --- |
| **No therapy** | **9INH**  (Completion 55%, Effectiveness 49.5%) | **4RIF**  (Completion 80%, Effectiveness 72%) | **60%** | **70%** | **80%** |
| 3% | 1.49% | 0.84% | 2,648 | 3,337 | 4,243 |
| 4% | 1.98% | 1.12% | 2,013 | 2,537 | 3,226 |
| 5% | 2.48% | 1.4% | 1,598 | 2,013 | 2,560 |
| **No therapy** | **9INH**  (Completion 50%, Effectiveness 45%) | **4RIF**  (Completion 80%, Effectiveness 72%) | **60%** | **70%** | **80%** |
| 3% | 1.65% | 0.84% | 1,809 | 2,279 | 2,898 |
| 4% | 2.20% | 1.12% | 1,357 | 1,709 | 2,173 |
| 5% | 2.75% | 1.40% | 1,086 | 1,368 | 1,739 |

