Members of the same household will be randomized to the same regimen. When cluster randomization is used, sample size must be adjusted accordingly because members of the same cluster are no longer independent observations 177. Usually, the required sample size is inflated by a factor of *1+(m–1)*ICC*; where *m* is the average cluster size and *ICC* is the intra-cluster correlation coefficient which denotes how similar subjects from the same cluster are with respect to their risk of developing the outcome, compared to those in other clusters 178. Given that the cluster sizes will vary (in Phase 2, 20% of subjects were household contacts, of whom 60% were single contacts, and 40%, or 8% of all participants, were in groups of 2-4 persons - with an average number of 2.5 contacts), we adjusted for this via the method described in 178. This calculates the design effect as**: *1+[(cv2+1)m-1]*ICC*** where ***cv*** is a ratio of the standard deviation of the cluster sizes, ***m*** and ***ICC*** as before. Even assuming an ICC as large as 0.1 (ICC is typically 0.05-0.12 for spouse pairs 179), this only results in a design effect of 1.03 - meaning a 3% increase to 2985 per group. Allowing for 10% loss to follow-up the number must be increased to 3283 per arm. Patients will continue to be followed even if they stop therapy themselves (i.e. non-compliance), or their physician stops therapy (e.g. pregnancy or adverse events). Because 847 subjects, enrolled in Phase 2 of this trial, are still being followed for occurrence of active TB using the same methods as proposed here, the total of number of new participants required in this phase can be reduced to 5720.

We have assumed 4RIF efficacy of 90%, based on available evidence. As shown below, if 50% of the 2,898 randomized to each group complete therapy and 28 months follow-up, this would provide more than 90% power, to confirm **non-inferior** efficacy of 4RIF, if the **non-inferiority** margin was 25% - equivalent to a minimum efficacy of 4RIF of 65%. (In other words, we would declare 4RIF **non-inferior** to 9INH if the efficacy of 4RIF was not more than 25% worse than 9INH.) This efficacy has been considered sufficient for authoritative recommendations of 6INH 107, 138, which has had efficacy of 40-69% in trials 33, 61, 65, 68, 104, 128.

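### Section 2.16 lets an undefined, data-driven judgement about household clustering decide the scale and variance method of the primary result; the numerical effect is small, but one analysis should be fixed in advance

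*Protocol*

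**What the plan says.** Section 2.16 first defines the primary analysis as an unadjusted Poisson marginal model fitted by GEE, with household as the cluster, an exchangeable correlation and log follow-up time as offset. Two conditional statements follow.

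- Branch A: "If clustering is significant we will calculate a rate ratio from the GEE Poisson regression".
- Branch B: "But if the effect of clustering is negligible, as anticipated, the proportion of subjects randomized to both treatment groups developing confirmed active TB" and a two-sided 95% confidence interval for the difference are estimated by an incidence density method, expressed per 1,000 person-years. No household term is mentioned.

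The section gives no test, significance level or ICC cut-off for choosing between the branches. Section 1.2 does not settle the measure either, since it speaks only of comparing cumulative incidence over 28 months.

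The clustering arises from the design. Section 2.11 states: "Members of the same household will be randomized to the same regimen". Section 2.3.3 says the same for household contacts, except that members enrolled later are randomised separately. Section 2.11 inflates the sample size by a design effect of 1.03, from 2,898 to 2,985 per group.

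**The concern.** One primary hypothesis has two possible primary results, on different scales and with different variance methods, and the trial's own data choose between them. The criterion is undefined, and its two sides are not complements: a correlation that is not statistically significant need not be negligible. Someone holding only the protocol cannot say whether the headline result will be a rate ratio or a rate difference, or which analysis supplies the p value for the interim threshold in section 2.17.1.

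The pre-test also has no clear purpose. Household members share a regimen because of how they were allocated, so a variance that respects the household is appropriate whatever the observed correlation. Section 2.11 has already paid for it; Branch B would drop that allowance at the analysis. A test based on few events in multi-person households may also miss clustering that is really there.

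**Working it through.** **1. The plan's own sample size.** Inputs from section 2.11 and Table S1: risks 1.65% (9INH) and 0.84% (4RIF), 80% power, "assuming alpha=0.05 and two-sided tests". The Poisson square-root formula is n = (1.960 + 0.842)² / [2(√p1 − √p2)²].

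- (√0.0165 − √0.0084)² = (0.12845 − 0.09165)² = 0.001354.
- n = 7.849 / (2 × 0.001354) = 2,898, as stated: "would be 2,898 participants with full follow-up in each group".
- 2,898 × 1.03 = 2,985, as stated.

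**2. Design effect from the stated household figures.** Section 2.11 reports from Phase 2 that 40% of household contacts, "or 8% of all participants, were in groups of 2-4 persons", averaging 2.5. Assume a household-size variance of 0.5, which the protocol does not give, so E[m²] = 6.25 + 0.5 = 6.75.

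- Mean size weighted by member = 6.75 / 2.5 = 2.7, so the design effect within these households at ICC 0.1 is 1 + 1.7 × 0.1 = 1.17.
- Overall: 0.92 + 0.08 × 1.17 = 1.014.

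The stated 1.03 is therefore slightly cautious. The range 1.014 to 1.03 is used below.

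**3. Cost of ignoring clustering.** The understatement of variance is 1 − 1/DE, and true two-sided alpha is 2[1 − Φ(1.96/√DE)].

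| Design effect | Variance understated | SE ratio √DE | True alpha | 95% CI coverage |
|---|---|---|---|---|
| 1.014 | 1.4% | 1.007 | 0.0516 | 94.8% |
| 1.03 | 2.9% | 1.015 | 0.0535 | 94.7% |
| 1.05 (assumed) | 4.8% | 1.025 | 0.0558 | 94.4% |
| 1.10 (assumed) | 9.1% | 1.049 | 0.0617 | 93.8% |

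By the step 2 method, the last two rows need about 30% and 60% of participants in multi-person households (0.70 + 0.30 × 1.17 = 1.051; 0.40 + 0.60 × 1.17 = 1.102). The protocol gives no such share.

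**4. Information available to a clustering test.** Mean risk is (1.65% + 0.84%)/2 = 1.245%. Total enrolment is 2 × 3,283 = 6,566.

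- Participants in multi-person households: 0.08 × 6,566 = 525. Expected events among them: 525 × 0.01245 = 6.5.
- Households: 525 / 2.5 = 210. With sizes 2, 3 and 4 assumed at 60/30/10%, pairs per household are (6.7 − 2.5)/2 = 2.1, giving about 441 pairs.
- P(both have TB) = p² + ICC × p(1 − p) = 0.000155 + 0.1 × 0.012295 = 0.00138 at ICC 0.1.
- Expected pairs with two events: 441 × 0.00138 = 0.61 at ICC 0.1, and 441 × 0.000155 = 0.07 at ICC 0.
- With 2 × 2,898 = 5,796 participants and the size variance of step 2, there are about 394 pairs; the figures are 0.55 and 0.06.

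By a Poisson approximation, the chance of at least one such pair is 1 − e^(−0.55) = 42% at ICC 0.1, against 1 − e^(−0.06) = 6% at ICC 0.

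**5. Simulation of the two-stage rule.** There were 10,000 trials per scenario, with beta-binomial households and full follow-up. Clustering was tested by a 5% moment test, an assumption because the protocol names none. The robust rate ratio used an independence working correlation.

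- With 8% in multi-person households and ICC 0.1, clustering was declared in 40% of trials, so about 60% took the unclustered branch.
- Type I error of the two-stage rule was 0.045 to 0.050 across ICC 0, 0.05 and 0.1 and household shares of 8%, 30% and 60% (Monte Carlo error about 0.004).
- With the 8% share, the branches gave different significance verdicts in 0.2-0.3% of null trials and 0.6% under the planned effect. The highest figure in any scenario was 1.5% (30% share, planned effect).

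**The case against.** The strongest reply is that section 2.16 does name one primary analysis, the GEE model, and that the conditional sentences only govern how the result is summarised. Both branches use the same intention-to-treat population, events and person-time. The switch depends on a nuisance quantity, the within-household correlation, and not on the treatment effect. The outcome is largely microbiological and judged by a panel blinded to regimen, so the open-label design adds little to the concern. A SAP could supply the test and threshold, and that Branch B ignores households is an inference.

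Much of this stands as a limit on size. It does not remove the point. The protocol is not silent here: it states a rule that changes both the effect scale and the method. A SAP that keeps the rule inherits the problem, and one that drops it departs from the protocol. The inference about Branch B is direct, since that branch applies only when clustering is judged negligible and names no household term.

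Two stronger readings are tempting. A reader might infer from the low expected count of two-event pairs that the test would almost always miss clustering. It would not: even one such pair is fairly strong evidence, and detection is about 40% under the assumed test. A reader might also infer a variance understatement of 5-10%. That needs 30-60% of participants in multi-person households. Section 2.11 expects many contacts at the international sites, but being a contact is not the same as being co-enrolled: 60% of household contacts in Phase 2 were single, and members enrolled later are randomised separately.

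**Conclusion.** The point holds as a pre-specification defect of moderate weight. The scale and variance method of the primary result depend on an undefined judgement made after the data are seen, although the clustering comes from the allocation and the sample size already allows for it.

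The documents do not support presenting this as a serious error-rate problem. At design effects of 1.014 to 1.03, ignoring clustering understates variance by about 1-3%, with true alpha about 0.052-0.054 and coverage about 94.7% at 1.03. The two-stage rule showed no material type I inflation.

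These figures rest on the Phase 2 share of 8%, ICC 0.1, the assumed household-size distribution and the assumed clustering test. The effect would be larger only if many more participants were in multi-person households, a share the protocol does not give for the new sites.

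**What to change.** Delete the conditional rule in section 2.16 and state one primary analysis, used whatever the observed correlation: the GEE Poisson model with log person-time offset and household-robust standard errors. Name one primary effect measure now, for example the rate ratio. Report the rate difference per 1,000 person-years, with the same household-robust standard errors, as a companion estimate.

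The cost is one paragraph of protocol wording and, at the plan's own design effect, a standard error up to about 1.5% wider than the unclustered one (√1.03 = 1.015). The sample size does not change, because the 2,985 per group already includes the allowance.

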**2.16.1 Justification**

Our planned primary analysis will be of study groups as randomized, i.e. an intention to treat analysis. This is recommended for superiority studies 166 because it provides a more conservative estimate of effect, since patients who did not take treatment per protocol are less likely to gain benefit. Hence differences between two regimens are attenuated making it more difficult to detect superiority.

**2.17 Frequency of Interim analysis and stopping rules**

**2.17.1 Primary outcomes**

Only one interim analysis of the primary outcome will be performed, one year after 33% of patients have been randomized. Further interim analyses, such as one year after 67% of subjects have been randomized, will fall too close to the end of randomization, to have any meaningful impact. We wish to avoid falsely concluding that one regimen has significantly superior effectiveness with this interim analysis – a well known risk 195, 196. Hence we will use a threshold of a p value <.001196, before concluding that 4RIF is significantly **inferior** to 9INH , and stopping the trial early.

